## 8.5 Programmatic deviation

Program deviation was defined as a failure to follow the study protocol.

8.5.1 Patient Informed Consent (PIC) is not approved by the Ethics Committee;

8.5.2 The patient did not sign the PIC and/or the patient and/or the investigator did not indicate the signing date;

8.5.3 The study-specific procedure occurred before the patient signed the PIC;

8.5.4 The Study required visit (IRV) was not conducted;

8.5.5 IRV through the window;

8.5.6 During the follow-up after surgery, no 24h electrocardiograms were performed or the records were interrupted, and 85% of the records were not kept at the monitoring window;

8.5.7 No TEE examination or data missing during follow-up after operation;

8.5.8 In case of scheme deviation, the CRF scheme deviation table shall be recorded. The person in charge of the study shall be notified after the CRF is completed.

Note: If protocol deviation occurs after enrollment, the deviation-related information should be recorded in the hospitalization record, and the deviation and study termination form should be recorded in the CRF immediately. The person in charge of the study shall be notified after the CRF is completed.

## 8.6 Enrollment

Enrollment took place after the screening of the patients or at the same time as the baseline visit. Patients were enrolled in the study when they met the inclusion criteria and did not meet the exclusion criteria.

8.6.1 Inform eligible patients of Study issues and provide written informed consent. The process of obtaining written informed consent must meet the requirements of the Helsinki Declaration, ISO14155-1 and local laws and regulations.

8.6.2 Written informed consent is signed and documented by both the patient/authorized person and the investigator.

## 8.7 Baseline visit

All baseline activities should be performed after the patient has been enrolled in the study and before undergoing a combined surgery for atrial fibrillation, and should not exceed 30 days after enrollment. At the baseline visit, the following baseline information should be collected from the hospitalization record or communication with the patient.

#### 8.7.1 Patient demographics and physical findings.

- ✓ Age.
- ✓ Gender.
- ✓ Recent height.
- ✓ Recent weight.
- ✓ Blood pressure.

#### 8.7.2 Patient's history of cardiovascular disease

- ✓ Recent New York Heart Association (NYHA);
- ✓ Left ventricular ejection fraction (LVEF), left atrial size and valvular heart disease measured by recent TEE or gated radionuclide examination;

#### 8.7.3 Patient cardiac medication

- ✓ Identify the classification of cardiac medications that the patient is currently taking; and
- ✓ Documentation of the patient's previous antiarrhythmic drug class for the treatment of atrial fibrillation; and
- ✓ Documentation of the patient's previous class of antithrombotic medications for the treatment of atrial fibrillation, including oral anticoagulants and/or antiplatelet aggregating agents.

#### 8.7.4 Patient history

- ✓ Documentation of co-morbid heart disease and cardiac surgery;
- ✓ Documentation of comorbid non-cardiac conditions.

#### 8.7.5 Patient's history of AF

- ✓ Record the date (year) of the patient's first episode of AF.
- ✓ Record the number of previous resuscitations for atrial arrhythmias.

- ✓ Documentation of the patient's arrhythmias other than atrial fibrillation.
- ✓ Evaluate CHA2DS2-VASc score and HAS-BLED score;

8.7.6 ECG information: provide recent ECG information (heart rate, rhythm, QT information, overall results);

8.7.7 Record the hospitalization records of the baseline visit and improve the baseline CRF. Try to notify the person in charge within 14 days of the visit. CRF must be authorized by the principal or representative.

Note: "Recent" means within the month of selection.

## **8.8 Combined Procedure for AF**

### **8.8.1 Procedure grouping**

This was a prospective, multicenter, randomized, 1:1 controlled study in which subjects underwent combined surgery for atrial fibrillation based on randomization to either ablation-first or block-first surgical strategies.

### **8.8.2 Randomization**

This was a multicenter, randomized, controlled, registry study in which all subjects who met the entry criteria were assigned a uniform serial number and computerized randomization by the core laboratory after signing a written informed consent form up to the time of surgery and were grouped according to the results of the randomization.

### **8.8.3 Procedure conditions**

All patients were in the cardiac electrophysiological catheter room. In a single operation, radiofrequency energy was used to conduct transcatheter atrial fibrillation catheter ablation under the guidance of Carto three-dimensional electroanatomic system; Under the guidance of X-ray and TEE, percutaneous LAAO was performed with a Watchman occluder.

### **8.8.4 Preoperative preparation**

#### **8.8.4.1 Preoperative Ultrasound Assessment**

Within 48 hours before operation, TEE or CTA (if the patient cannot tolerate TEE probe insertion) should be performed to exclude left atrial or LAA thrombus, and abnormal pulmonary vein stenosis. If a thrombus is found, the operation should be postponed until the thrombus is

eliminated. At the same time, the left atrial diameter and the effective working depth of LAA should meet the inclusion criteria.

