### 4.2 Inclusion criteria

4.2.1 Age  $\geq 18$  years;

4.2.2 Symptomatic, nonvalvular atrial fibrillation ;

4.2.3 Refractory to the treatment of antiarrhythmic drugs;

4.2.4 Based on the CHA2DS2-VASc scoring system (stroke risk assessment for patients with nonvalvular atrial fibrillation), a score of  $\geq 2$  ( $\geq 3$  for females) and one of the following :

4.2.4.1 Unsuitable for long-term standardized anticoagulation therapy;

4.2.4.2 Thromboembolic events despite long-term standardized anticoagulation therapy;

4.2.4.3 According to the HAS-BLED scoring system (bleeding risk assessment for patients with nonvalvular atrial fibrillation), scoring  $\geq 3$  points.

4.2.5 Preoperative imaging examinations such as TEE or computed tomography angiography (CTA) assess that the maximum diameter of the ostium at each angle of the LAA is  $\leq 30$ mm, and the estimated effective working depth of the LAA is not less than the maximum diameter of the ostium;

4.2.6 The maximum anteroposterior diameter of the left atrium is  $\leq 55$  mm by transthoracic echocardiography (TTE) before operation;

4.2.7 Subjects or authorized family members voluntarily accept the clinical trial and sign a written informed consent.

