### 4.3 Exclusion criteria

- 4.3.1 Congenital heart disease, valvular heart disease, angina pectoris, myocardial infarction, myocarditis, cardiomyopathy, pulmonary heart disease, serious infections, autoimmune diseases, diseases of the blood system, malignant tumors; and
- 4.3.2 Combination of other arrhythmias, such as atrioventricular tachycardia, atrioventricular nodal tachycardia, preexcitation syndrome, atrioventricular block, and sick sinus node syndrome.
- 4.3.3 Previous history of percutaneous coronary intervention or transcatheter RFCA/cryoablation for atrial fibrillation;
- 4.3.4 Heart function (New York Heart Association Function Classification, NYHA) Class III or above, or left ventricular ejection fraction (LVEF) shown by color Doppler echocardiography  $\leq 35\%$ ;
- 4.3.5 Left atrial or LAA thrombus (confirmed by TEE or CTA);
- 4.3.6 Presence of serious neurological disorders (neurological infections, etc.), mental disorders (including substance abuse, chronic alcoholism, etc.).
- 4.3.7 Abnormalities of thyroid function not controlled by combined medications; and
- 4.3.8 Complicated with abnormal liver function (AST or ALT > 3 times the upper limit of normal) or abnormal renal function (SCR > 3.5mg/dl or CCr < 30ml/min);
- 4.3.9 History of cardiac surgery within the last 6 months;
- 4.3.10 Contraindications to radiofrequency ablation procedures (e.g., pregnancy status, allergy to contrast media, etc.).
- 4.3.11 A life expectancy of less than 12 months;
- 4.3.12 Participation in other clinical studies within 3 months prior to the date of informed consent, or ongoing participation in other clinical studies.

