### 4.4 Abscission criteria

- 4.4.1 Enrolled patients failed to complete treatment by the enrolled treatment program due to lack of efficacy of drugs, cost of treatment, and unsuccessful surgery.
- 4.4.2 Failure to complete TEE and dynamic electrocardiogram examination at the specified time point.

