4.5.2 Incomplete clinical information affects the judgment of test results; and

4.5.3 Intracardiac echocardiography (ICE) is used instead of TEE to guide surgery and follow-up assessment due to intolerance of TEE examination during and after surgery.

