#### 8.8.7.3 LAA occlusion

Select the appropriate Watchman occluder according to the LAA measurement size.

Under the protection and guidance of a pigtail catheter, deliver the delivery sheath of the occluder to LAA, and confirm the position of the sheath through angiography. Withdraw the pigtail catheter, send it into the pre-installed Watchman occluder, and lock the delivery sheath with the guide sheath. Under the monitoring of X-ray or TEE, the self-expanding occluder can be expanded by fixing the handle and removing the sheath. Confirm the position of the occluder and whether there is an obvious marginal shunt through angiography, and measure the compression ratio under the maximum lateral diameter of the occluder. The stability of the occluder was confirmed by the tug test. The presence of PDL and the maximum shunt size were evaluated by TEE multi-angle color Doppler blood flow.

When the occlusion position is not satisfactory, the release position of the occluder can be readjusted through recovery (full recovery/half recovery/micro recovery) and re-release operation under X-ray and/or TEE monitoring. If the adjustment is invalid, consider replacing the plug with a different size.

When the occlusion is satisfactory, release the device.

TEE assessed pericardial effusion.

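### Patients who cannot tolerate TEE may enter on CTA, yet after randomisation a missed or replaced TEE is a ground for drop-out or removal

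*Protocol*

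**What the plan says.** **Entry and preparation.** Inclusion criterion 4.2.5 reads "Preoperative imaging examinations such as TEE or computed tomography angiography (CTA) assess" the appendage dimensions, so either modality qualifies a patient. Exclusion criterion 4.3.5 likewise accepts TEE or CTA for thrombus. Section 8.8.4.1 gives the reason for the alternative: "TEE or CTA (if the patient cannot tolerate TEE probe insertion) should be performed to exclude left atrial or LAA thrombus". None of 4.3.1 to 4.3.12 names TEE contraindication or intolerance.

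**At operation.** Section 8.8.3 states "Under the guidance of X-ray and TEE, percutaneous LAAO was performed with a Watchman occluder". Section 8.8.7.3 adds "The presence of PDL and the maximum shunt size were evaluated by TEE multi-angle color Doppler blood flow". Section 8.8.7.5 makes TEE the intraoperative ultrasound method, to limit measurement heterogeneity; its clause on ICE is garbled.

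**At day 45.** Table 1 and Appendix C list TEE. Section 5.2.5 allows TEE or CTA.

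**Consequences.** Abscission criterion 4.4.2 is "Failure to complete TEE and dynamic electrocardiogram examination at the specified time point". Removal criterion 4.5.3 applies when ICE "is used instead of TEE to guide surgery and follow-up assessment due to intolerance of TEE examination during and after surgery". Section 8.5.7 counts a missing follow-up TEE as a deviation.

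**Order of events.** Under Table 1 and 8.8.2, randomisation takes place after consent and at any time up to surgery. All of these consequences therefore fall after allocation.

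**The concern.** The same characteristic is accommodated at entry and is a route out of the study later. A patient who cannot accept the probe can satisfy every entry rule on CTA and be randomised. That patient then meets rules that recognise only TEE.

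Two things are at stake. The first is the randomised comparison. Excluding a patient before allocation costs nothing in validity, whereas removing one afterwards, on an event that happens during or after the assigned procedure, does. The second is measurement. Device-related thrombus is a component of the primary endpoint (3.1), and 8.9.3.7 places it, together with peri-device leak, in the TEE follow-up of the occluder. Keeping a patient in the analysis does not recover a TEE that was never done, and a CTA in its place may not be comparable. The background section gives leak and device thrombus as reasons for the trial, so this is the imaging it can least afford to lose.

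**Working it through.** **Step 1. Imaging rules side by side**

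| Time point | Accepted imaging | Consequence if TEE is absent |
|---|---|---|
| Eligibility (4.2.5, 4.3.5) | TEE or CTA | none |
| Within 48 hours before operation (8.8.4.1) | TEE, or CTA if the probe is not tolerated | none |
| Operation (8.8.3, 8.8.7.3, 8.8.7.5) | TEE | removal if ICE replaces it for intolerance (4.5.3) |
| Day 45 (Table 1, Appendix C) | TEE | abscission (4.4.2), deviation (8.5.7) |
| Day 45 (5.2.5) | TEE or CTA | none stated, but 4.4.2 and 8.5.7 still recognise only TEE |

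A patient followed by CTA at day 45, as 5.2.5 allows, still meets 4.4.2 and 8.5.7 as written. Section 5.2.5 is thus another passage to reconcile and does not settle the matter.

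**Step 2. The plan's own figure**

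Section 7 gives 71 evaluable per group, 20% loss and a minimum of 89 per group, with 101 planned.

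- 71 / (1 − 0.20) = 88.75, rounded up to 89. This reproduces the stated figure.
- The 71 itself cannot be reproduced, because Section 7 states no effect size, standard deviation or event rates.

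**Step 3. Number affected**

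The protocol gives no share of TEE-intolerant candidates. Assuming 1% to 5%:

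- 101 × 0.01 = 1.0 per arm
- 101 × 0.05 = 5.1 per arm

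**Step 4. Effect on evaluable numbers**

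After the planned 20% loss, 101 × 0.80 = 80.8 per arm remain. Let f be the extra share removed. It can be applied after that loss, 80.8 × (1 − f), or added to it, 101 × (0.80 − f).

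| f | After the 20% | Added to the 20% |
|---|---|---|
| 1% | 80.0 | 79.8 |
| 5% | 76.8 | 75.8 |
| 10% | 72.7 | 70.7 |
| 15% | 68.7 | 65.7 |

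The number falls below 71 only when f exceeds 0.80 − 71/101 = 9.7% (added) or 1 − 71/80.8 = 12.1% (applied after). Across 1% to 5% it stays above 71 on either reckoning.

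**Step 5. When intolerance becomes known**

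The imaging in 8.8.4.1 falls within 48 hours before operation, and randomisation may precede it. Intolerance can therefore be established before allocation, but nothing in the protocol requires that it be.

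**The case against.** A reader might infer that every such patient is certain to be lost. The text does not support that:

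- Section 5.2.5 permits CTA at day 45.
- Section 8.8.5 allows general anaesthesia when the suggested scheme is not tolerated, so intolerance of the probe beforehand need not persist during the operation.
- Section 4.5.3 is triggered by ICE replacing TEE, not by a CTA before surgery.
- Section 8.8.7.2 speaks of centres that use TEE for guidance, and 8.8.7.3 also checks marginal shunt by angiography. The TEE requirement at operation is thus worded inconsistently.
- The other primary components (stroke or TIA, bleeding, cardiovascular death, rehospitalisation) need no TEE.

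Nor does the protocol show an intention to randomise patients who will be lost. It shows entry and removal rules that were not aligned.

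A reader might also infer differential loss, because 8.8.5 suggests deep sedation for ablation but only local anaesthesia for occlusion, and the order of the two is what is randomised. That is conjecture. Intolerance already present at baseline is balanced between arms in expectation. An arm effect would need intolerance that first shows itself during surgery, and a screening criterion would not catch that.

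It can also be argued that the fault lies in the removal rules alone and that a new exclusion narrows the population needlessly. This stands in part: analysing such patients as randomised is needed whatever the entry rule. It does not supply the missing TEE, however, and for intolerance already known that can only be dealt with before allocation or by a stated alternative assessment.

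**Conclusion.** The conflict is in the protocol's own text: TEE intolerance is allowed for at entry, no exclusion covers it, and later rules make a missed or replaced TEE a ground for drop-out, removal or deviation. The result is a foreseeable, not certain, risk of post-randomisation exclusion or of a missing or non-comparable assessment of device thrombus and leak.

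The number is probably small, about 1 to 5 per arm, but this rests on an assumed 1% to 5% because the protocol gives no rate. At that rate at least 75.8 per arm remain after the planned 20% loss, above 71, so no size shortfall is shown. The point is worth acting on because the loss is avoidable, affects a primary component and is cheap to prevent.

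**What to change.** 1. Establish ability to undergo TEE before the serial number is assigned, and list known TEE contraindication or intolerance at screening in 4.3.
2. Reconcile 4.2.5, 4.3.5, 5.2.5, 8.5.7, 8.8.4.1, Table 1 and Appendix C on which imaging is accepted at each time point.
3. Keep any patient found TEE-intolerant after randomisation in the analysis as randomised, instead of removing them under 4.4.2 or 4.5.3, and record the TEE assessment as missing or as made by another modality.

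The cost is one added criterion, some aligned wording and a slightly smaller eligible pool. If the sponsor prefers not to narrow the population, the alternative is to admit these patients with a stated alternative assessment and to amend 4.4.2, 4.5.3 and 8.5.7 accordingly. The price is then less comparable device imaging in those patients.

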#### 8.8.4.2 Anti-arrhythmic drugs

Stop using AAD except amiodarone for at least 5 half-lives before operation, and stop using amiodarone for at least 1 month before operation.

#### 8.8.4.3 Preoperative anticoagulation regimen

Take warfarin and effective anticoagulation for 3-4 weeks before admission (the international standardized ratio INR is controlled at 2.0-3.0) or take a new oral anticoagulant (NOAC, including rivaroxaban tablets or dabigatran capsules);

#### 8.8.4.4 Perioperative anticoagulation regimen

For patients who take warfarin orally before operation, if effective anticoagulation is maintained before operation (the international standardized ratio INR is controlled at 2.0-3.0), warfarin may not be stopped during perioperative period; It is recommended to replace anticoagulant drugs for patients with atrial fibrillation according to the guidelines for those who fail to meet the anticoagulation standards, guide them to use NOACs anticoagulation or choose low-molecular-weight heparin needle instead; For patients reusing NOACs, stop using the new oral anticoagulant once before the operation. If no oral anticoagulant contraindication is confirmed 12 hours after the operation (such as moderate or above pericardial effusion), restart the anticoagulant treatment of NOACs.

#### 8.8.4.5 Other preparations

Fasting for 8 hours and drinking for 6 hours before operation; Bilateral inguinal skin preparation; Indwelling catheter when necessary; If the "steel ball method" is used to guide the LAAO operation, a steel ball with a diameter of 1cm should be attached to the third and fourth intercostals on the left edge of the sternum before the operation as a reference for intraoperative measurement.

#### 8.8.5 Anesthesia program

Each center chooses the anesthesia scheme individually according to the patient's condition and the center's routine operation. It is suggested that local anesthesia plus deep sedation should be used for atrial fibrillation ablation; Local anesthesia is recommended for LAAO. If the patient's condition cannot tolerate the above scheme, general anesthesia can be selected.

## 8.8.6 Surgical protocols for the ablation-first group

### 8.8.6.1 Preparation for ablation

A deca-polar electrode catheter was placed in the coronary sinus (CS) through the subclavian vein or femoral vein. Under the guidance of an X-ray image and/or TEE, an atrial septal puncture was performed. After a successful puncture, continuous anticoagulation was performed in the vein, and ACT was maintained for 250~350s. Under the guidance of the Carto3 electrolytic mapping system, use a multipolar mapping catheter or ablation catheter to reconstruct the three-dimensional model of the left atrium, and under the guidance of a three-dimensional mapping system and/or pulmonary phlebography, combined with the characteristic potential of pulmonary vein vestibule, confirm the position of pulmonary vein vestibule.

### 8.8.6.2 Atrial Fibrillation Ablation Procedures

For paroxysmal atrial fibrillation, bilateral pulmonary vein isolation (PVI) was performed, and a single circle isolation rate was recorded. The mapping and ablation of spontaneous and/or induced (atrial high-frequency stimulation or intravenous injection of isoproterenol) non-pulmonary vein trigger focus were followed. Verify bilateral pulmonary vein bidirectional conduction block. For spontaneous or induced atrial fibrillation during operation, and ablation or intravenous injection of AAD (such as amiodarone needle or ibutilide needle) can not convert to sinus rhythm, synchronous DC cardioversion is performed.

For non-paroxysmal atrial fibrillation (persistent atrial fibrillation and long-term persistent atrial fibrillation), bilateral PVI was performed and the single circle isolation rate was recorded. The ablation of non-pulmonary vein trigger focus and individualized improvement of the left atrial matrix were performed. Specific matrix improvement strategy can refer to "STABLE-SR" matrix improvement strategy LAA electrical isolation is feasible for patients with a clear trigger focus of LAA Verify bilateral pulmonary veins and bidirectional conduction block of each ablation line. For spontaneous or induced atrial fibrillation during operation, and ablation or intravenous injection of AAD (such as amiodarone needle or ibutilide needle) can not convert to sinus rhythm, synchronous DC cardioversion is performed.

### 8.8.6.3 Recommended ablation parameters

It is recommended to choose an open saline-irrigated perfusion catheter (such as ThermoCool SmartTouch catheter [Biosense Webster, Diamond Bar, CA]) for ablation. The ablation energy is 30~40W, the ablation mode is recommended to be power mode, and the flow rate of cold brine is

recommended to be 17~30ml/min. The details shall be subject to the routine operation settings of each center.

For centers with AI software modules, it is recommended to individually select AI target values for each part of the atrium based on the experience of the center; The ablation endpoint of a single ablation focus can also be selected in combination with other relevant parameters such as catheter pressure and impedance change.

Since the ThermoCool SmartTouch SF catheter has not yet been popularized in China, it is not recommended to use the "short-term, high-power" ablation strategy based on the catheter.

#### 8.8.6.4 Atrial Fibrillation Ablation Endpoints

Electrical isolation of the pulmonary veins from the left atrium was achieved bilaterally, with no possibility of inducing intrapulmonary venous or non-pulmonary venous triggering foci, and bidirectional conduction block was achieved on both sides of the ablation lines, and sinus rhythm was converted and maintained pharmacologically or by synchronized direct-current resuscitation.

